### 3.4 Initial Interview and Baseline Data

Once informed written consent has been obtained, each participant will undergo an initial interview with a RA. A detailed data collection form/questionnaire will be used during the interview to further confirm the patients' eligibility for the study and to gather baseline data. Data gathered during the interview will include information on the participants' smoking habits, previous attempts at smoking cessation and current willingness/confidence to quit.

A caution is indicated for a number of conditions in the product information sheets of varenicline and NRT lozenges. These include diabetes mellitus, renal or hepatic impairment, gastrointestinal disease, history of seizures, psychiatric illness, pregnancy, breastfeeding and cardiovascular symptoms including myocardial infarction or stroke. A detailed medical history (current medical conditions and medications) including the presence of any contraindications or cautionary conditions will be sought during the interview. The interview will also involve an assessment of the presence of any psychological symptoms using the Patient Health Questionnaire (PHQ-9).

The NRT lozenges used in this study are sugar-free but not the placebo lozenges. Smokers with a history of diabetes will not be excluded from the study but will be counselled on the need to be vigilant and perform regular self-monitoring of blood glucose levels. The final decision to include or exclude patients with diabetes will remain with the treating medical team.

Participants with any exclusion criterion including any contraindications to varenicline or NRT lozenges will be excluded from the study and will be referred to Quitline for smoking cessation support. Those participants who are noted to have a cautionary condition (without any exclusion criterion) will be referred to an in-house clinician for further assessment. The decision on whether to include participants who have a cautionary condition is at the discretion of the treating medical team and the RA based on an evaluation of the potential risks and benefits from a patient's participation in the study. In the event of any uncertainties, the expert opinion of site coordinators will be sought.

During the baseline interview, the RA will also seek the participants' consent to contact their regular General Practitioners (GP) and Community Pharmacist (CP) to inform them of the participants' involvement in the study. This will be important to ensure the safe and appropriate delivery of healthcare services to the participant. Once written consent is obtained, the RA will contact the respective GP and CP via a telephone, email or fax.

Information regarding the participants' involvement in the project will also be noted on the hospital discharge summary.

### 3.5 Study treatments

There are two treatment arms in this study. All participants will be randomised to one of two treatment arms. The allocated study medications will be provided free of charge.

#### Brands to be used

|                  |                       |
|------------------|-----------------------|
| Varenicline      | Champix™              |
| NRT lozenges     | Nicaway™ 2mg lozenges |
| Placebo lozenges | Mint lozenges         |

NRT and placebo lozenges will be purchased in bulk and repackaged and labelled in sachets, each containing two lozenges.. Distribution of varenicline and repackaged lozenges will take place from Barwon Health or Symbion to the other four hospitals (study sites). All participants will be provided with 12 weeks supply of varenicline and 200 lozenges on recruitment. Renewal supplies of trial lozenges (nicotine and placebo) will be delivered to participants on their request.

It is still possible that participants with prior experience in using NRT, especially the NRT lozenges (Perrigo Inc) distinguish the active and placebo lozenges solely based on taste and texture; it will be acknowledged as one of the limitations of the study.

#### 3.5.1 Intervention Arm

Participants in the intervention arm will receive varenicline plus NRT (lozenges) for 12 weeks. An additional 12 weeks course of varenicline will be provided (i.e. 24 weeks in total) to those who need further support (to be determined by the staff in charge of delivering the intervention based on participant's nicotine dependence, adherence to treatment, and any adverse events]. NRT lozenges/placebo will also be provided to those needing further support.

#### 3.5.2 Comparator Arm

Participants in this arm of the study will receive varenicline plus NRT placebo (mint) lozenges for 12 weeks with an additional 12 weeks course of varenicline provided to those needing further support (i.e. 24 weeks in total).

#### 3.5.3 Dosing Schedules

Varenicline standard dosing schedule derived from the varenicline Product Information sheet (14)

| Treatment days | Dosage                       |
|----------------|------------------------------|
| 1 – 3          | One 0.5mg tablet once daily  |
| 4 – 7          | One 0.5mg tablet twice daily |

|             |                            |
|-------------|----------------------------|
| 8 – onwards | One 1mg tablet twice daily |
|-------------|----------------------------|

Participants will receive varenicline immediately after randomisation and will be informed to start the medication soon after they receive it. All participants will be asked to completely abstain from smoking if possible or at least reduce their smoking over the first seven days of the varenicline course and to aim to quit completely within one to two weeks of starting. Along with the medication, participants will also be given Consumer Medicines Information (CMI) sheets highlighting key information about the dosing schedule and important adverse effects to be aware of. A trained RA will give clear verbal counselling to the participants along with a lozenge instruction sheet which explains how to use the lozenges, the most common side effects, emergency contact details and information on how to obtain a renewal of their medication.

If a participant experiences severe or intolerable nausea from varenicline, a RA will check their method of administration (i.e. how they take the tablets in relation to food and water) and if needed reduce the dose as recommended by the Australian Medicines Handbook 2018 and Varenicline Product Information Sheets.

#### **NRT and Placebo Lozenges dosing schedule**

##### **Instructions for use of lozenges derived from Perrigo product information sheet (15)**

Lozenge (NRT or mint) should be taken only when there is an urge to smoke. Take a lozenge (2 mg) as required when you have an urge to smoke up to every 1-2 hours as needed. You must not use more than 15 lozenges in a day.

1. Place one lozenge on the tongue and suck until the taste becomes strong
2. Rest the lozenge between the gum and cheek
3. When the taste fades start sucking the lozenge again
4. Repeat this process until the lozenge completely dissolves (it takes about 30 minutes)

Participants will receive NRT or placebo lozenges immediately after randomisation (i.e. at the same time as varenicline). They will be informed to start the medication (or placebo) soon after they receive it. As with varenicline, participants will receive a Consumer Medicines Information (CMI) sheet and a lozenge instruction sheet highlighting key information about the lozenges including information on how to take the lozenges and some common side effects of which to be aware. A trained RA will give clear verbal counselling to the participants along with a lozenge instruction sheet which explains how to use the lozenges, the most common side effects, emergency contact details and information on how to obtain a renewal of their medication.

### **3.6 Quitline Support and Text Messages**

Participants will be informed and encouraged to use behavioural support from Quitline as per Quitline standard protocols. Using Quitline support is not a requirement for participation in the study.

Participants will be sent automated text messages once a week for the first month of treatment, then once every month. Text messages will be sent by Quitline or by the RA using the ClickSend system. Text messages will reinforce the importance of adherence to the study medications, long-term abstinence and also contain emergency contact details for the participants. Participants who do not have a cell phone will be called on their land phone by the RA instead of sending text messages.

### 3.7 Concomitant Treatments

All participants are encouraged to inform their GPs and CPs about their participation in this study upon discharge from hospital to ensure a safe delivery of healthcare services. Throughout the study, participants will be able to take any medication as required, except for smoking cessation medications. Use of concomitant medication will be recorded at each of the study follow-ups and checked for potential interactions. The use of other smoking cessation medications including other forms of NRTs (i.e. patches or gums) is strongly discouraged during the course of the study to ensure patient safety. If a participant uses other smoking cessation medication during the study period, an appropriate record of this will be maintained. Their results will still be included in the primary and secondary analyses, however, sensitivity analysis will be performed by excluding them from the primary analysis.

### 3.8 Follow-up Interviews

Five follow-up interviews will be conducted over the entire course of the study: at weeks one and three of treatment initiation and at three-, six- and twelve- months from treatment initiation. The one- and three- week follow up interviews will be done by the RA involved in the participant's recruitment. These follow-ups will be conducted face-to-face for participants who are still inpatients or via telephone for participants who have been discharged. Participants who are uncontactable via telephone will be sent text messages and emails for their follow-ups. Three-, six- and twelve-month follow-up interviews will be conducted via telephone by an independent RA who is blinded to treatment allocation and who was not involved in the participant's recruitment.. A total of ten attempts will be made to contact the participant for follow-up interviews. Participants' next of kin will also be contacted if the RAs are unable to reach the participants directly. If a participant is unable to be contacted beyond this point they will be noted as 'lost to follow-up' and they will be considered as "smokers" according to the Russell Standard. Participants who successfully complete follow-ups at 3, 6 and 12 months will be reimbursed for their time via a gift voucher that will be provided at the 12-month follow-up.

#### 3.8.1 Follow-up 1: One-week from treatment initiation

For participants who are still inpatients this interview will be done in hospital, for those who have been discharged it will be done over the telephone. The purpose of this follow-up is to check adherence to treatment medication, any adverse effects experienced and answer any participant queries. Withdrawal symptoms may be more predominant at this stage, increasing the chance of relapse. Participants may also be more inclined to use concomitant non-evidence based smoking cessation approaches such as e-cigarettes, or use additional medications such as NRT patches or gums to circumvent the withdrawal symptoms and reduce cravings. Participants will be asked about their use of such medications and details will be recorded.

### 3.8.1 Follow-up 2: Three-weeks from treatment initiation

For participants who are still inpatients, this interview will be done in hospital, for those who have been discharged it will be done over the telephone. The focus of this follow-up is to monitor participants' response to the study medications. Data will be collected on the side effects experienced, potentially from the use of the study medications, adherence to the study medications, the presence of any withdrawal symptoms, cravings and relapses and any changes in the participant's medical conditions or medications.

### 3.8.3 Follow-up 3: Three-months from treatment initiation

This follow-up will be done by a RA (blinded to treatment allocation) over the phone three months after the participant has been discharged from hospital. This follow-up will gather information on patient adherence to treatment medication, adverse effects experienced, presence of any withdrawal symptoms, cravings and relapses.

### 3.8.4 Follow-up 4: Six-months from treatment initiation

A RA (blinded to treatment allocation) will contact the participants at six months from hospital discharge. Participant self-reports of treatment adherence, adverse effects, withdrawal symptoms and cravings will be recorded. The number of Quitline calls made throughout the treatment period will also be recorded as well as the use of any other forms of behavioural/pharmacotherapy. Participants meeting the self-reported abstinence criteria (see 3.9.2) will be asked where they would like to take the CO breath test i.e. in hospital or by having a RA visit them at home.

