### 3.1 Inclusion Criteria

Adults aged 18 years or over, admitted to participating hospitals with a history of smoking  $\geq$  10 cigarettes per day on average in the four weeks prior to their hospital admission, interested in quitting smoking, willing to use pharmacotherapy and available for a 6 months follow-up post-discharge and willing/capable to provide signed informed consent will be eligible for the study. This study will not recruit any outpatient smokers. Hospitalisation

provides a great opportunity for initiating smoking cessation interventions, firstly because of the 'smoke free' policies in all study sites facilitating quitting, and secondly due to greater patient receptiveness to smoking cessation messages and interventions at a time of perceived vulnerability to negative health outcomes. Moreover, initiation of smoking cessation medications such as varenicline during hospital stay allows close monitoring of patients for any adverse events.

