### 3.9.2 Primary Outcome Measure

The primary outcome will be biochemically verified continuous abstinence from 2 weeks to 6 months from treatment initiation. A 2-week period will be allowed on treatment commencement to match the recommendation in the varenicline product information sheet. Participants who self-report abstinence (i.e. self-report smoking no more than five cigarettes, including the use of non-combustible tobacco products and electronic cigarettes) over this period (i.e. weeks 2-26) will be asked to perform a carbon monoxide (CO) breath test. CO levels will be measured by trained RAs blinded to treatment allocation, using using a hand held piCO+ Smokerlyzer (Bedfont Scientific, Maidstone, Kent, UK) during a hospital or home visit. Participants with a CO level <10ppm will be considered abstinent. Sensitivity analysis will be performed using a lower CO cut-off of <5ppm.

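### The protocol gives conflicting time origins for the 3- and 6-month contacts, so the CO test for the primary outcome may fall after week 26 by each participant's remaining hospital stay

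*Combined protocol and SAP*

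**What the plan says.** Three time origins appear for the same contacts.

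- **Treatment initiation.** Protocol section 3.8 places the later interviews "at three-, six- and twelve- months from treatment initiation". The headings agree: "Follow-up 3: Three-months from treatment initiation" and "Follow-up 4: Six-months from treatment initiation". Section 3.9.2 defines the primary outcome as "biochemically verified continuous abstinence from 2 weeks to 6 months from treatment initiation", and says that those who report abstinence "over this period (i.e. weeks 2-26) will be asked to perform a carbon monoxide (CO) breath test".
- **Hospital discharge.** Under those same headings, section 3.8.3 sets the 3-month call at "three months after the participant has been discharged from hospital", and section 3.8.4 says the research assistant "will contact the participants at six months from hospital discharge". The inclusion criterion in section 3.1 asks that participants be "available for a 6 months follow-up post-discharge".
- **Two weeks after the start of treatment.** The contents list shows this origin in its titles for the 3- and 6-month contacts.

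The 12-month contact (section 3.8.5) is tied to treatment initiation in its heading, and its body gives no discharge date. No visit window is stated for any contact. SAP Tables 2 and 6 run from 2 weeks to 3, 6 and 12 months without saying from what date.

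**The concern.** Section 3.5.3 has varenicline handed to inpatients straight after randomisation, to be started soon afterwards. Treatment initiation therefore usually precedes discharge, and the two dates differ by the rest of the hospital stay. Staff cannot follow both rules.

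The conflict falls on the contact that matters most. The 6-month call identifies the self-reported abstainers who go on to the CO test, and section 4.2 counts a self-report without biochemical validation as smoking. If the discharge rule is applied, two things follow:

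- A participant abstinent through week 26 who relapses before a later CO test can be scored a smoker on the primary outcome.
- The 7-day point-prevalence outcomes in section 3.9.3 look back from the day of follow-up, so they move entirely with the visit.

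For participants given the optional second 12 weeks of varenicline, the time off treatment at assessment would also vary with length of stay.

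**Working it through.** **The plan's own figure.** The sample size is not in dispute, but it supplies the rates used below. Inputs from section 4.1: 23% in the control arm, a difference of 15 points (so 38%), 5% significance and 80% power. Section 4.2 makes the test two-sided. The mean rate is 0.305.

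- Without continuity correction: n = [1.96 × √(2 × 0.305 × 0.695) + 0.8416 × √(0.23 × 0.77 + 0.38 × 0.62)]² / 0.15² = 146.7, so 147 per arm.
- With continuity correction: (146.7 / 4) × [1 + √(1 + 4 / (146.7 × 0.15))]² = 159.8, so 160 per arm. This matches the plan.
- Power at 160 per arm, uncorrected test: 83.3%.

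**Timing under each origin.** With treatment initiation as origin, the contacts fall at about weeks 13 and 26. With the origin in the contents list, they fall at about 13 + 2 = 15 and 26 + 2 = 28. With discharge as origin, and the first dose taken before discharge:

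week of contact = 26 (or 13) + days from first dose to discharge / 7

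The documents give no length of stay, so the gap below is an assumed range. Section 3.8 provides for participants still in hospital at the three-week interview, so 21 days is possible but not shown to be typical.

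| Gap (days, assumed) | 3-month contact (week) | 6-month contact (week) |
|---|---|---|
| 1 | 13.1 | 26.1 |
| 3 | 13.4 | 26.4 |
| 7 | 14 | 27 |
| 14 | 15 | 28 |
| 21 | 16 | 29 |
| 28 | 17 | 30 |

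**Illustration of the effect.** Suppose a share h of abstainers relapses per extra week, equally in both arms, and every participant is assessed w weeks late. Each rate is multiplied by (1 − h)^w. The documents give no relapse rate, so h is assumed. Power at 160 per arm, uncorrected test, starting from 83.3%:

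| h per week (assumed) | w = 1 | w = 3 | w = 4 |
|---|---|---|---|
| 0.5% | 83.1% | 82.5% | 82.2% |
| 1% | 82.8% | 81.7% | 81.1% |
| 2% | 82.2% | 80.0% | 78.9% |

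At h = 1% and w = 3, the rates become 22.32% and 36.87%, and the difference shrinks from 15 to 14.55 points. In people, three weeks at 0.5% to 1% is about 1.5% to 3% of abstainers. That is 160 × 0.23 × 1.5% = 0.6 at the low end and 160 × 0.38 × 3% = 1.8 at the high end, per arm, and only if everyone were three weeks late.

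**The case against.** The strongest reply is that most of the protocol counts from treatment initiation: section 3.8, the headings of 3.8.3 and 3.8.4, and the outcome definitions in 3.9.2 and 3.9.3. The discharge sentences may be leftover wording. The contents list carries different titles for the same sections, which suggests that this part was reworded. Nothing in the documents gives the discharge sentences precedence. Some lag would also exist under any origin, since up to ten contact attempts are allowed and the CO visit is arranged after the call.

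Much of this stands, and it rules out several stronger readings.

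- A reader might infer that the primary outcome is measured at a different week in each participant. That follows only if the discharge rule was applied, and even then short stays move the contact by days.
- A reader might infer that the abstinence window itself drifts. Section 3.9.2 fixes it at weeks 2 to 26. What would move is the interview and the CO test.
- A reader might object that the interval between the 6- and 12-month contacts would vary. No listed outcome or SAP analysis uses that interval.

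The reply does not remove the contradiction, and it does not deal with relapse between week 26 and a late CO test. Ordinary scheduling lag is a reason to state a window, not a reason to leave the origin open.

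**Conclusion.** The inconsistency is real, sits in current operative text, and reaches the visit at which the primary outcome is ascertained. It should be reconciled. If the discharge wording is followed, assessment falls after week 26 by the stay remaining after the first dose.

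The likely effect is small: a loss of 0.2 to 1.1 percentage points of power for a one-week delay in everyone, at assumed relapse of 0.5% to 2% per week. Larger losses need long stays in nearly all participants. These figures rest on assumed stays and relapse rates, on equal relapse in both arms, and on the planning rates of 23% and 38%.

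A reader might also infer a biased comparison between arms. The documents do not support that: the scheduling rule is the same in both arms, and randomisation should balance the remaining stay on average. The harm is an ambiguous endpoint date, some added variability and a slight dilution. The documents do not show which origin the sites used.

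**What to change.** **Protocol.** Use one origin, treatment initiation, in sections 3.8.3 and 3.8.4, the inclusion criterion and the contents list, to match the weeks 2 to 26 outcome. Define it as the recorded date of the first varenicline dose, or the randomisation or dispensing date where the first dose was not recorded. Dispensing and first dose are not the same event, so state which was used. Add a visit window for the 6-month call and the CO test.

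**SAP.**

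- Name the same origin and derive self-reported abstinence over weeks 2 to 26 from it, whenever the call took place.
- Report the actual week of the 6-month call and of the CO test by arm.
- Add a sensitivity analysis of the primary outcome restricted to CO tests inside the window. Say beforehand whether self-reported abstainers tested outside it are set aside or counted as smokers. This analysis is needed because re-deriving self-report cannot correct a late CO result.

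**Cost.** Short wording changes, one derived date, one descriptive table and one extra analysis. The sample size stays at 160 per arm. The SAP describes recruitment as complete, so if the 6-month calls have already been made, the useful steps are to state which origin the sites used and to make the SAP changes.

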## 2. Aim and Objectives

This study aims to evaluate the effectiveness and safety of the combination of varenicline and NRT lozenges at assisting achievement of abstinence amongst heavy smokers admitted to six 'smoke-free' public hospitals in Australia.

The primary objective of the study is to compare biochemically-verified continuous abstinence in hospitalised smokers treated using varenicline plus NRT lozenge versus varenicline monotherapy.

The secondary objectives of this study are to compare:

- Self-reported 7-day point prevalence abstinence and continuous abstinence in the two treatment arms from 2 weeks to 3, 6 and 12 months after treatment initiation
- CO verified 7-day point prevalence abstinence at 6 and 12 months from treatment initiation for participants who self-report abstinence at these follow-ups
- Self-reported treatment adherence and adverse events to the study medicines at all follow-ups as well as the number of Quitline sessions attended after treatment initiation

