### 3.9.3 Secondary Outcome Measures

The secondary outcome measures are:

- Self-reported continuous abstinence from 2 weeks to three-, six- and twelve- months from treatment initiation
- CO verified continuous abstinence from 2 weeks to 12 months from treatment initiation for participants who self-report abstinence at this follow-up
- Self-reported 7-day point prevalence abstinence (i.e. smoking not even a puff in the past 7 days on the day of follow-up) measured from 2 weeks to 3, 6 and 12 months from treatment initiation
- CO verified 7-day point prevalence abstinence from 2 weeks to 6 and 12 months from treatment initiation for participants who self-report abstinence at these follow-ups
- Participant self-reports of withdrawal symptoms and cravings using the Mood and Physical Symptoms Scale (MPSS)
- Self-report of treatment adherence using the 8-item Tool for Adherence Behaviour Screening (TABS)
- Adverse events experienced from study medications
- Change in psychological distress
- Number of Quitline sessions attended/received
- Other health resources used including emergency department visits, GP visits (for smoking cessation), over-the-counter medicines used as well as the use of other smoking cessation therapies and alternate products

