**Table 2: Smoking abstinence rates by treatment groups from 2 weeks to 3, 6 and 12 months**

| Outcome                                         | Intervention
n (%) | Control
n (%) | P-value | Odds
ratio
(95%
CI) | Adjusted
odds ratio
(95%CI) |
|-------------------------------------------------|-----------------------|------------------|----------------|------------------------------|-----------------------------------|
| Smoking abstinence at 3-months           |                       |                  |                |                              |                                   |
| Self-reported prolonged abstinence              |                       |                  |                |                              |                                   |
| Self-reported 7-day point prevalence abstinence |                       |                  |                |                              |                                   |
| Smoking abstinence at 6-months           |                       |                  |                |                              |                                   |
| Biochemically verified prolonged abstinence     |                       |                  |                |                              |                                   |
| Self-reported prolonged abstinence              |                       |                  |                |                              |                                   |
| Self-reported 7-day point prevalence abstinence |                       |                  |                |                              |                                   |
| Smoking abstinence at 12-months          |                       |                  |                |                              |                                   |
| Biochemically verified prolonged abstinence     |                       |                  |                |                              |                                   |
| Self-reported prolonged abstinence              |                       |                  |                |                              |                                   |
| Self-reported 7-day point prevalence abstinence |                       |                  |                |                              |                                   |

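### The visit sections send only continuous abstainers for the CO test, which conflicts with the listed CO-verified 7-day point prevalence outcome and leaves it under-ascertained

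*Combined protocol and SAP*

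**What the plan says.** Protocol 3.8.4 (6 months) gives the instruction for the CO test: "Participants meeting the self-reported abstinence criteria (see 3.9.2) will be asked where they would like to take the CO breath test". Protocol 3.8.5 (12 months) uses the same sentence and the same cross-reference.

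Section 3.9.2 contains a single self-report criterion, "self-report smoking no more than five cigarettes, including the use of non-combustible tobacco products and electronic cigarettes". Those who meet it "over this period (i.e. weeks 2-26) will be asked to perform a carbon monoxide (CO) breath test". The cut-off follows: "Participants with a CO level <10ppm will be considered abstinent", with a sensitivity analysis at <5 ppm.

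The 7-day definition is in 3.9.3, which neither visit section cites: "smoking not even a puff in the past 7 days on the day of follow-up". The same section lists as a secondary outcome "CO verified 7-day point prevalence abstinence from 2 weeks to 6 and 12 months from treatment initiation". The matching objective in section 2 says that verification is "for participants who self-report abstinence at these follow-ups", without saying which kind of abstinence.

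Protocol 4.2 counts self-reported abstinence without biochemical validation as smoking. In SAP Tables 2 and 6, the only 7-day rows are labelled "Self-reported 7-day point prevalence abstinence". Biochemically verified rows exist for prolonged abstinence only.

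**The concern.** Point prevalence is worth reporting beside continuous abstinence because it picks up people who quit late, or who relapsed and recovered. These are the people whom the visit instructions leave untested. Someone who smoked more than five cigarettes in month 3 and then stopped for good satisfies the 7-day definition at 6 months but fails the 3.9.2 criterion. Site staff following 3.8.4 would not arrange a CO test, and the analysis rule would then code the participant as a smoker.

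A stated secondary outcome would therefore be misclassified in one direction for a definable group, and would add little to the primary outcome. The omission from the SAP tables adds a second problem: the outcome could disappear from the report without explanation.

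**Working it through.** **The plan's own figure.** The only stated number nearby is the sample size. Protocol 4.1 gives 23% against 38% (23% + 15 points), 80% power and 5% significance, which 4.2 makes two-sided.

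- Mean proportion: (0.23 + 0.38)/2 = 0.305.
- Uncorrected n = [1.960 × √(2 × 0.305 × 0.695) + 0.842 × √(0.23 × 0.77 + 0.38 × 0.62)]² / 0.15² ≈ 146.7, rounded up to 147 per arm.
- With continuity correction: (146.7/4) × [1 + √(1 + 4/(146.7 × 0.15))]² ≈ 159.8, rounded up to 160 per arm.

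The stated 160 is reproduced. It concerns the primary outcome, and nothing below changes it.

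**Set logic at 6 months.** Let A = meets the 3.9.2 self-report criterion, B = no puff in the past 7 days, V = CO <10 ppm.

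- Primary outcome = A and V.
- CO-verified 7-day point prevalence as defined in 3.9.3 = B and V.
- If only A is tested and untested participants count as smokers, the recorded outcome is A and B and V. This is a subset of A and V, so it cannot exceed the primary outcome.
- The group lost is B and V but not A: late quitters, and those who relapsed and quit again.

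This assumes that <10 ppm also applies to point prevalence; no separate cut-off is stated. A and B are not nested, because A permits up to five cigarettes and B permits none.

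**12 months.** Two readings are possible.

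- Criterion kept at weeks 2-26, as 3.9.2 says: someone who met it but missed or failed the 6-month CO test can still be verified at 12 months, so the bound against the primary outcome is not strict. Someone who relapsed after week 26 and quit again is tested; someone who relapsed before week 26 and quit again is not.
- Criterion extended to 12 months: verified 7-day point prevalence is bounded by verified continuous abstinence to 12 months.

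The first reading does not match the window of the 12-month continuous outcome in 3.9.3. The second is not what the cross-reference says.

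**Scale (assumed inputs).** The documents give no point-prevalence rate. Take verified continuous abstinence at the planning rates (38% and 23%), let a = 0-10% of continuous abstainers have had a puff in the last 7 days, and let e = 5-15% of an arm be 7-day abstinent with CO <10 ppm but outside the 3.9.2 criterion.

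| | Intervention | Control |
|---|---|---|
| Recorded if only A is tested: C × (1 − a) | 0.38 × 0.90 to 0.38 = 34.2-38.0% | 0.23 × 0.90 to 0.23 = 20.7-23.0% |
| If all 7-day abstainers are tested: C × (1 − a) + e | 39.2-53.0% | 25.7-38.0% |
| Coded as smokers: 160 × e | 8-24 | 8-24 |

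**Arm comparison (a = 0).** Testing only A gives 38% against 23%: 15 points, OR (0.38/0.62)/(0.23/0.77) = 2.05. Testing all 7-day abstainers:

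- e = 5% intervention, 10% control: 43% against 33%, 10 points, OR 1.53.
- e = 10% intervention, 5% control: 48% against 28%, 20 points, OR 2.37.

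The distortion can go either way, and its direction cannot be known from the documents.

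**The case against.** The strongest reply is that nothing in the protocol restricts the CO test to continuous abstainers in so many words. Attached to a 7-day outcome, the wording in sections 2 and 3.9.3 most naturally means those who report 7-day abstinence at the visit. On that reading everyone relevant is tested and the cross-reference in 3.8.4 and 3.8.5 is merely loose. This stands as far as it goes: the documents conflict, and they do not prove that anyone went untested. But 3.8.4 and 3.8.5 are the sections that direct the visits, and they point to a criterion that excludes these participants, so reconciliation is needed on either reading.

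The impact is also limited. The primary outcome is untouched, and late quitters still appear in the self-reported 7-day outcome at 3, 6 and 12 months, which has table rows. That is correct, and it keeps this a secondary-outcome matter.

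A reader might go further and infer that verified point prevalence cannot be measured at all, or that it can never exceed the primary outcome at any visit. Neither follows. It is measured in the tested subset, and the bound is strict only at 6 months with a shared cut-off. Nor can a fixed fraction of point-prevalence abstainers be said to be lost, because the documents supply no rate.

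**Conclusion.** The point holds as a conflict between the visit instructions and the outcome list, together with an omission from the SAP tables. Followed literally, 3.8.4, 3.8.5 and 3.9.2, combined with the rule in 4.2, under-ascertain CO-verified 7-day point prevalence at both visits. The 12-month trigger also carries the wrong window for continuous abstinence to 12 months. The missing rows in SAP Tables 2 and 6 are a defect however the trigger is read.

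The figure of 8-24 per arm rests wholly on the assumed 5-15%, and on those participants attending and passing the test. It shows scale and is not an estimate. The change should be made, but the integrity of the primary analysis does not depend on it.

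**What to change.** - In 3.8.4 and 3.8.5, state that anyone reporting either continuous abstinence to that follow-up or no smoking in the past 7 days is asked for the CO test.
- In 3.8.5, define continuous abstinence from 2 weeks to 12 months instead of borrowing weeks 2-26.
- State the CO cut-off for point prevalence.
- Add CO-verified 7-day rows at 6 and 12 months to SAP Tables 2 and 6.

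The cost is extra CO visits with the existing staff and device, plus travel reimbursement under 3.12. Under the assumed 5-15% this is at most 320 × 0.05 to 320 × 0.15 = 16-48 visits at each time point.

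The SAP describes recruitment in the past tense, so it may be too late to change the trigger. If follow-up is complete, report by arm how many 7-day self-reported abstainers were not CO tested and label the outcome as verified only in the tested subset, or declare it dropped and give the reason. That costs wording and one tabulation.
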